## Abstract

**Background:**

Addressing the enhancement of ill health self-management skills in adults diagnosed with bipolar disorder may be considered an important intervention for health care systems worldwide.

**Objective:**

This protocol describes the study “Management of my Bipolarity” (MoB), which aims to develop an educational intervention for adults with bipolar disorder and assess its effectiveness. The objectives include (a) a literature review on bipolar disorder educational interventions; (b) a qualitative exploration of the educational needs of people with bipolar disorder; (c) development of an educational intervention based on objectives (a) and (b) (ie, the MoB educational intervention); and (d) exploration of the effectiveness of the intervention regarding participants’ knowledge of their mental health condition and enhancement of their ill health self-management skills. The MoB educational intervention will consist of an in-person and a web-based intervention in the form of a digital platform.

**Methods:**

The proposed interventional study is a combination of a qualitative and a quantitative design (mixed methods study). A focus group and content analysis will be implemented for the qualitative assessment of the educational needs of adults with bipolar disorder. The intervention will be developed based on the qualitative data of the study and relevant literature. The effectiveness of the acquired knowledge and self-management skills will be assessed according to (a) substance use behavior, (b) health locus of control, (c) impulse control, (d) adherence to pharmacotherapy, (e) relapse prevention, (f) improvement of quality of life, and (g) bipolar disorder knowledge level via structured instruments in the quantitative part of the study using descriptive and inferential statistics (SPSS version 24.0).

**Results:**

A total of 13 patients with bipolar disorder have been interviewed (8 women, 5 men) to identify educational needs to be covered through the intervention. Moreover, a literature review on bipolar disorder educational interventions has been completed. These data have been incorporated in the design of the MoB in-person intervention and the digital platform. The digital platform is live, and the development of the MoB in-person intervention was completed at the end of 2020. The recruitment of the participants for the intervention (40 patients) and the control group (40 patients) began during the first semester of 2021. Moreover, by tracking the platform for 1.5 years, we have recorded that 2180 users have visited the platform with an average session duration of almost 2 minutes. Mobile and tablet devices are being used by 70% of the visitors.

**Conclusions:**

Since new parameters regarding educational interventions will be explored, these findings are expected to provide evidence that participation in structured educational interventions offers patients the opportunity to improve adherence to pharmacotherapy and increase their quality of life.

**Trial Registration:**

ClinicalTrials.gov NCT04643210; https://clinicaltrials.gov/ct2/show/NCT04643210

**International Registered Report Identifier (IRRID):**

DERR1-10.2196/25168

## Introduction

Bipolar disorder (BD) is one of the main causes of disability, affecting approximately 45 million people globally [1,2]. The percentage of people with mood disorders, including BD, in Cyprus is approximately 13.8%, and the incidence per year of people with BD is approximately 0.6% [3]. The most prominent manifestations of BD (ie, cognitive, mood, and interpersonal deficiencies) are all linked with decreased quality of life [4,5]. Therefore, BD has a significant effect on the personal, social, and professional lives of both patients and their families/significant others [6,7]. Most importantly, BD is linked to high mortality rates due to suicide, as well as comorbidities with other types of illness (eg, cardiovascular disease) [8-10]. All of the above highlight the need for support and empowerment of people with BD as one of the key objectives of health care systems worldwide [11].

Empowerment in the context of health care emerges out of the promotion of independence of service users and the restriction of disability and incapacitation, at both personal and social levels [12]. One of the main methods of empowering people with chronic illness is through reinforcement of their capacity to manage the illness themselves (ie, self-management capacity) [12], while reducing health care professionals’ involvement to the minimum possible [13]. Enhancement of ill health self-management capacity is achieved through educational and training interventions [14]. Educational interventions, as therapeutic approaches, include information intake and training in skills regarding the ability to effectively deal with ill health issues such as self-monitoring of symptoms, medication adherence, or fulfillment of daily needs [14,15]. A plethora of positive effects have been associated with enhancement of ill health self-management skills through educational interventions, such as decreased frequency and duration of relapse episodes and hospitalization, and improvement of quality of life [14]. Educational interventions for self-management of disease symptoms have been described for chronic mental diseases, including psychosis and BD [16,17]. Computer software applications have also been incorporated in educational interventions aiming to increase knowledge and health literacy [18,19]. Specifically, web-based interventions present certain advantages such as more opportunities for participation, as they are available throughout the day and provide accessibility to a larger network of people, establishing this method of training as one with a significant financial advantage [20,21]. Moreover, participation in web-based educational interventions may be more favorable for people encountering the social stigma of mental illness, on national and international levels [22,23].

Although previous data support the effectiveness of structured educational interventions for people with BD, the data remain insufficient regarding relevant interventions in northern European countries, including Cyprus, as well as in relation to combined in-person and web-based interventions [14]. Specifically, there are no relevant structured interventions available in the Greek language. In addition, to the best of our knowledge, only one study reported to date used a combination of in-person training alongside a respective web-based intervention [24]. Although numerous digital educational interventions and relevant platforms for BD exist, the degree to which they have been developed according to any theoretical background or empirical data on the needs of patients is not clear. Notably, no digital platforms aiming to increase the knowledge and educate people in BD or enhance relevant ill health self-management skills have been found in the Greek language, and the implementation of such interventions appears to be almost absent in the health care systems of Greece and Cyprus.

Previous data support difficulty in impulse control [25], and high rates of substance use [26] and nonadherence to pharmacotherapy [27] in people diagnosed with BD, which are all linked to increased relapse rates and decreased quality of life [4,5]. Thus, interventions, mainly psychotherapeutic, toward addressing these issues need to be further explored [28]; the combination of in-person and web-based interventions is highly recommended for effective management of symptoms [29]. Other studies support that performance of ill health self-management skills is associated with one’s self-perception about the health-related locus of control and related health literacy level [30,31]. Overall, educational interventions targeted to people with chronic disorders, including BD, should constitute a basic service offered by health care systems and mental health service structures at the international level [11].

The proposed protocol focuses on a study aiming to develop an educational intervention for patients with BD, and explores the null hypothesis that patients who solely receive pharmacotherapy will show the same improvement in important aspects of their lives, such as relapse rate and quality of life, compared to those who receive pharmacotherapy and structured educational interventions. The effectiveness of the proposed intervention will be tested in relation to improvement with respect to (a) impulse control, (b) substance use attitudes, (c) adherence to pharmacotherapy, (d) relapse prevention, (e) BD knowledge level, and (f) self-perceived quality of life and locus of health-related control. Thus, the findings of the proposed study are expected to provide data on the effectiveness of a structured educational intervention, which combines in-person and digital interventions, regarding enhancement of ill health self-management skills.

## Methods

### Aim

The aim of the study entitled “Management of my Bipolarity,” hereafter referred to as MoB, is to develop and test an educational intervention for patients with BD. The stages of the study include: (1) a literature review on BD educational interventions; (2) exploration of the educational needs of adults with BD; (3) development of the MoB educational intervention, encompassing in-person sessions and a digital platform; and (4) exploration of the effectiveness of the MoB intervention in adults diagnosed with BD regarding (i) their knowledge about this disorder, and (ii) the empowerment of ill health self-management skills in relation to the improvement of impulse control, adherence to pharmacotherapy, relapse frequency, quality of life, and substance use attitudes.

### Design

This study is based on a mixed method design and consists of four stages.

Stage 1 includes a qualitative exploration of the educational needs of patients, aiming to develop an experimental educational intervention according to these needs. Moreover, a literature review on BD educational interventions was performed in this stage to support this objective according to the steps described by Tawfik et al [32] for systematic reviews. Stage 1 has been completed.

Stage 2 includes the design of the MoB intervention both in person and with the digital platform. The design of the in-person intervention relies on the Colom and Vieta [33] model, in which cognitive behavioral techniques are incorporated according to existing literature [34] and the results of Stage 1 (all relevant findings of the literature review and data acquired in the qualitative research of educational needs). The structure of the MoB digital platform has been designed by the researchers of this study and a web developer, partially based on the preferences and needs of the participants (as determined in Stage 1). Stage 2 has also been completed. The digital platform will be further enriched based on the qualitative and quantitative findings from platform evaluation techniques and interactive educational features in Stage 4.

Stage 3 includes implementation of the MoB in-person educational intervention and the quantitative evaluation of its effectiveness regarding the acquired knowledge and self-management skills of the participants at four time points (ongoing).

Stage 4 includes the qualitative and quantitative assessment of the applicability of the digital platform (ongoing).

### Settings and Sampling

The target population is adults diagnosed with BD who are under treatment. The recruitment will be implemented in collaboration with the mental health services used by the participants. Specifically, both private and public mental health services in Cyprus have been informed about the objectives and procedures of the study through a specific communication process. Through this process, several patients have already been referred to the research team by their psychiatrists/therapeutic team coordinator to participate in Stage 1. As a result, convenience sampling will be combined with snowball sampling, according to study inclusion criteria set in every stage. The study is also posted on social media and groups related to BD (health care service users, health care professionals).

To promote participant retention, an action plan has been developed. Specifically, the principal investigator (AH) will arrange one or two social meetings with the participants of Stage 1 and Stage 3 to achieve some degree of intimacy, emphasize confidentiality, and ensure engagement with the study. The cost of these social meetings is covered by the Nursing Department of Cyprus University of Technology. Regarding the control group of Stage 3, the principal investigator (AH) will also make a phone call once or twice per month to reassure their participation in the study, as follows: “Hello, I am [name] from the MoB project. I’m calling to see how you are, and if you are still interested in participating in the project. The next appointment will be on date X. Is this okay with you, or do you have any other arrangements for the day?”

### Stage 1

#### Objectives

The objective of Stage 1 is to perform a literature review on BP educational interventions and define the educational needs of adults with BD via empirical exploration of their living experience, aiming to integrate data in the MoB intervention. This stage has been completed. Specifically, the objectives of the systematic review included exploration of the educational methods applied to individuals with BD and their effectiveness regarding enhancement of ill-health self-management skills in relation to (i) relapse prevention, (ii) adherence to pharmacotherapy, and (iii) enhanced quality of life. This stage also evaluated the BD literacy needs in people with BD. An additional objective of the review was to inform the design of Stage 3 regarding eligible outcome measures for assessment of the effectiveness of the proposed intervention.

An advanced search in the CINAHL Medline, Scopus, Psych INFO, and Cochrane Library databases was performed between December 2018 and June 2020 by two researchers (MK and AH). The following key words were used singly and in combination: “bipolar disorder,” “manic-depress*,” “mania,” “depress*,” “education*,” “self-management,” “intervention,” “program*,” “empowerment,” “psycho-education,” “e-health,” and “literacy.” The following inclusion criteria were set: (a) an empirical, quantitative study; and (b) published in the English language in a peer-reviewed journal between 2007 and 2020. The methodological accuracy of the included studies was assessed with the Health Evidence Quality Assessment Tool [35].

#### Inclusion Criteria and Sampling for Qualitative Exploration of Patients’ Educational Needs

The inclusion criteria were set as follows: (a) sufficient experience (more than 6 months) as a patient under BD treatment; (b) willingness to communicate the living experience of BD; and (c) ability to reflect on the living experience of BD, as it will be drawn from the narrative content [36]. The final sample size was based on theoretical and data saturation of emergent themes [37-39].

#### Data Collection and Analysis

The form of the data collection interview, focus group or personal interview, was designed to be assigned according to the participant’s convenience. Since Cyprus is a small island with approximately 1 million citizens, some of the participants were reluctant to participate in focus group discussions due to the social stigma of mental illness [40]. Participation in personal interviews was expected to preserve their anonymity.

A semistructured guide with open-ended questions, set up by the research team according to relevant literature, was used for data collection in this stage. The interview guide included the following questions:

Please tell us what you know about your mental health condition/BD.Please describe what you would like to know about bipolar disorders.Please describe in what way and on what topics you would like to be educated and increase your knowledge on bipolar disorders?Please describe your expectations from an educational intervention regarding its impact on your everyday living.Would you like this intervention to be implemented one-on-one or in a group?How long would you like the intervention to last?What is your level of engagement with the internet?Are you familiar with computer use?

The original intention was to have two focus groups (6-10 people per group); however, in the process of the research, only one focus group was ultimately deemed to be necessary. The focus group participants met two to three times. In the second meeting, the themes revealed in the first meeting were verified and enriched where possible. During the third meeting, the researchers interpreted the data, followed by a discussion with the participants. This method was also applied to personal interviews (2-3 meetings with each participant). Data analysis was based on the conventional mode of content analysis [41].

### Stage 2

The purpose of the development of the ΜoΒ in-person intervention is to create an applicable, feasible, and effective intervention to enhance BD knowledge and ill-health self-management skills in people diagnosed with BD. Specifically, a textbook has been devised explaining in detail the step-by-step process and the techniques of the experimental educational method of the MoB in-person intervention.

The goal of the development of the MoB digital platform is to create an ecosystem where people with BD will be educated and empowered to make use of the platform via a computer, tablet, or mobile phone. The owner of the platform is the Nursing Department of Cyprus University of Technology and the administrator is the principal investigator (AH). The participants of the proposed study will have the opportunity to access the platform during and after completion of the study.

### Stage 3

#### Inclusion and Exclusion Criteria

The following inclusion criteria have been set for participation in the MoB intervention: (1) clinical diagnosis based on the Diagnostic and Statistical Manual of Mental Disorders-5 for BD; (2) aged between 18 and 65 years; (3) signed the informed consent form; (4) stable mood status at the beginning of the MoB in-person intervention based on clinical assessment, conducted by the principal investigator (AH); (5) experience of the illness for at least 1 year based on the medical record; (6) adequate awareness of the illness, based on the following guide: (a) are you aware of the reason(s) you are using mental health services/under medication? and (b) are you aware of the aim of the educational intervention in which you may participate?; and (7) familiarity with computer use.

The exclusion criteria are: (1) intellectual disability (IQ<70), based on the Wechsler Adult Intelligence Scale [42]; (2) brain damage (eg, following a stroke) based on diagnostic tests; (3) acute phase of the illness, based on clinical assessment and use of the Young Mania Rating Scale (YMRS; total score <12) [43] and/or Beck Depression Inventory (total score <17) [44]; and (4) substance use problems at the beginning of this stage according to the Alcohol Use Disorders Identification Test (AUDIT; total score <9) [45] and Drug Use Disorders Identification Test (DUDIT; total score <2 for women or <6 for men) [46].

All eligible participants will be randomly assigned (in terms of gender, age, duration of illness) into the intervention group and the control (waiting) group. With the aim of obtaining a moderate correlation effect, with 80% statistical power and .05 level of statistical significance, 40 participants are needed in the intervention group and 40 participants are needed in the control (waiting) group.

The criteria for discontinuing participation in the intervention group are disorder relapse and nonadherence to pharmacotherapy (discontinuation of medication).

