The degree of self-perceived quality of life will be measured by the total score in the WHOQOL scale assessment. This is a 1-5 Likert-type scale including 26 items. The minimum score in the scale is 26 and the maximum is 130; higher scores indicate a better outcome. The BD level of knowledge will be measured by the total score in the BDKS. This is a 25-item, true-false scale. The items address diagnosis, etiology, disease course, symptoms, treatment, and life impact BD-related knowledge. The ratio of “true” to “false” responses is assessed; a higher percentage of correct values indicates a better outcome. The degree of ability to control impulses will be measured by the total score in the YMRS. This is a 0-4 Likert scale, including 11 items. The total score of the scale ranges from 0 to 44; a lower total score indicates a better outcome. The degree of adherence to pharmacotherapy will be measured by the total score in the DAI-30. This is a 30-item true-false scale. The ratio of “true” to “false” responses is assessed; a higher percentage of correct values indicates a better outcome. Drug use will be measured by the total score in the DUDIT scale. This is a 1-5 Likert, 11-item scale (total score range: 1-55); a lower total score indicates a better outcome. Alcohol use will be measured by the total score in the AUDIT. This is a 0-4 Likert, 10-item scale (total score range: 0-40); lower scores indicate a better outcome. The degree of self-perceived health-related locus of control will be assessed by the MHLC tool, which is a 6-point Likert (scored from 1 to 6), 18-item scale (Form A). These items are grouped in three subscales corresponding to three different loci of control (ie, internal, others, and fate/luck); higher sum scores in each of the 3 subscales indicate a stronger locus of control. The frequency of relapses will be measured by the number of hospitalizations after completion of the in-person intervention. The number of hospitalizations will be measured as the sum of individual hospitalizations in a high-security psychiatric hospital/setting; the lower the number of hospitalizations, the better the outcome. The duration of relapses will be assessed by the duration of inpatient hospitalizations in days after completion of the in-person intervention. The duration of inpatient hospitalizations will be measured as the sum of the days of hospitalization in a high-security psychiatric hospital/setting; the lower the duration in days of hospitalization, the better the outcome.

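### The score conditions in exclusion criteria 3 and 4 point to the wrong end of the scales for their own labels, and the stated DUDIT range contradicts the stated DUDIT item scoring

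*Protocol article*

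**What the plan says.** All of the eligibility text is in the protocol article, Methods, Stage 3, Inclusion and Exclusion Criteria. Inclusion criterion 4 asks for "stable mood status at the beginning of the MoB in-person intervention".

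The exclusion list then contains:

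- criterion 1: "intellectual disability (IQ<70), based on the Wechsler Adult Intelligence Scale"
- criterion 3: "acute phase of the illness, based on clinical assessment and use of the Young Mania Rating Scale (YMRS; total score <12", joined by and/or to "Beck Depression Inventory (total score <17"
- criterion 4: "substance use problems at the beginning of this stage according to the Alcohol Use Disorders Identification Test (AUDIT; total score <9" and "DUDIT; total score <2 for women or <6 for men"

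The section Effectiveness Evaluation describes the scales as outcome measures. It gives YMRS as 0-44, AUDIT as 0-40 and WHOQOL as 26-130. It says of the DUDIT: "This is a 1-5 Likert, 11-item scale (total score range: 1-55". For YMRS, AUDIT and DUDIT it states that lower totals are better. It gives no direction for the Beck inventory, which is used only for eligibility.

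**The concern.** An exclusion criterion should describe the patients who are kept out. Here the labels describe unwell patients or patients with substance use problems, while the attached score conditions describe the opposite end of the scales. A reader cannot apply both parts of the criterion to the same patient.

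The DUDIT has a second fault. Its stated range cannot arise from its stated item scoring, so it is unclear which coding the eligibility cut-offs refer to. The DUDIT is used both to decide entry and as an outcome.

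These criteria decide who is randomised, and the article's Results section (Stage 3) says that recruitment began in the first semester of 2021. Screening may therefore already rest on an interpretation that the text does not record. An auditor or a replicating team could not verify from the article which rule was applied.

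**Working it through.** **Inputs.** Cut-offs come from Inclusion and Exclusion Criteria. Item counts, item scoring, ranges and directions come from Effectiveness Evaluation.

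**Step 1: reproduce the stated ranges.** For a sum score, minimum = items x lowest item score and maximum = items x highest item score.

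| Scale | Items and scoring | Computed range | Stated range | Agrees |
|---|---|---|---|---|
| YMRS | 11 items, 0-4 | 11 x 0 = 0 to 11 x 4 = 44 | 0-44 | yes |
| AUDIT | 10 items, 0-4 | 10 x 0 = 0 to 10 x 4 = 40 | 0-40 | yes |
| WHOQOL | 26 items, 1-5 | 26 x 1 = 26 to 26 x 5 = 130 | 26-130 | yes |
| DUDIT | 11 items, 1-5 | 11 x 1 = 11 to 11 x 5 = 55 | 1-55 | maximum only |

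Three of the four ranges reproduce. Only the DUDIT minimum fails.

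**Step 2: which totals the score conditions select as written.**

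- YMRS below 12: totals 0-11, which is 12 of 45 possible values.
- AUDIT below 9: totals 0-8, which is 9 of 41.
- DUDIT on the stated range 1-55: below 2 gives the single total 1 (1 of 55); below 6 gives totals 1-5 (5 of 55).
- DUDIT on the range implied by the item scoring, 11-55: none of 45 for either cut-off.

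**Step 3: compare with the rest of the text.** For YMRS, AUDIT and DUDIT the selected end is the one that the article calls better. This conflicts with the labels of criteria 3 and 4. For the mood scales it also conflicts with inclusion criterion 4. In exclusion criterion 1 of the same list, the less-than sign on IQ marks the values that exclude, so the list offers no convention under which the later signs mean the reverse. For the Beck inventory the conflict rests on the label and on inclusion criterion 4 only, since no direction is stated.

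**Step 4: does reversing the sign repair the DUDIT criterion?** On 11-55, at least 2 and at least 6 are each met by 45 of 45 totals. With item scoring 1-5, reversing the sign alone would turn a criterion that no total meets into one that every total meets. The sign and the coding have to be settled together.

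**The case against.** The strongest defence is that the intent is recoverable. The labels are clear, criterion 3 rests on clinical assessment as well as scores, and inclusion criterion 4 separately requires stable mood. The figures in parentheses may be the scores allowed for entry. That is plausible, and staff may well apply it so. But the text does not say it, and the IQ criterion in the same list uses the sign in the opposite sense.

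Several stronger readings are tempting, and the defence is right to resist them:

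- **That the rule removes every stable patient.** A reader might infer this, but criterion 3 names acute illness judged partly by clinical assessment, and a patient judged stable is not in an acute phase. What can be said is that the score conditions flag the low totals.
- **That the DUDIT cut-offs cannot be reached on the plan's stated range.** They can: 1-55 contains totals below 2 and below 6. They are out of reach only on 11-55, the range that the item scoring implies. On that range the DUDIT condition as printed excludes nobody, so a claim that non-users are screened out would have to rest on the AUDIT.
- **That the and/or connector is itself wrong.** As an exclusion joining mania and depression scores, it is unobjectionable. It becomes a problem only if the clause is re-read as an entry condition, and stable mood would still be required separately.
- **That raters would differ.** The only assessor named for mood status is the principal investigator, and no multi-rater screening is described.
- **That the DUDIT outcome comparison is damaged.** If one coding is the other plus 1 per item, totals differ by a constant 11 x 1 = 11. Group differences and changes from baseline are then unaffected. The harm is confined to the eligibility threshold and to the reported level of the score.

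**Conclusion.** The point holds in two parts.

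First, the score conditions in exclusion criteria 3 and 4 contradict their labels, the stable-mood requirement, the sign convention of the IQ criterion and, for three of the four scales, the article's own scoring direction. Taken literally they flag YMRS 0-11 and AUDIT 0-8.

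Second, the DUDIT range of 1-55 is wrong for 11 items scored 1-5. That scoring gives 11-55, on which none of the 45 totals meets the printed cut-offs and all 45 would meet the reversed ones.

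The first part rests on reading the list as it is headed, as exclusions. The second assumes that the DUDIT total is the plain sum of its items, as the article's other ranges imply. Neither part depends on the sample size or on any analysis choice. The documents do not show that anyone was wrongly admitted or refused, and they do not settle which cut-off values or which DUDIT coding is correct. Because the text fixes eligibility and recruitment has started, it should be corrected and not left to interpretation.

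**What to change.** Reconcile Inclusion and Exclusion Criteria with Effectiveness Evaluation:

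1. For each score condition (YMRS, Beck, AUDIT, DUDIT), state whether it marks patients who may enter or patients who are excluded. Write the inequality to match, and say on which side the boundary value falls.
2. Make the connector between conditions agree with that choice.
3. State one DUDIT item coding with its correct range, use it for both eligibility and the outcome, and confirm that the sex-specific cut-offs refer to that coding.
4. Check participants already screened against the corrected rule, and document any who were admitted or refused in conflict with it.

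The sponsor has to confirm the cut-off values themselves; this review does not choose them. The cost is a protocol text correction and a review of existing screening records. Sample size, visits and analysis are not affected.
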